## Abstract

**Introduction:**

The high prevalence and severity of depression in adolescents with polycystic ovary syndrome (PCOS) is a critical health threat that must be taken seriously. The identification of high-risk groups for depression in adolescents with PCOS is essential to preventing its development and improving its prognosis. At present, the routine screening of depression in adolescents with PCOS is mainly performed using scales, and there is no early identification method for high-risk groups of PCOS depression in adolescents. It is necessary to use a warning model to identify high-risk groups for depression with PCOS in adolescents.

**Methods and analysis:**

Model development and validation will be conducted using a retrospective study. The study will involve normal adolescent girls as the control group and adolescent PCOS patients as the experimental group. We will collect not only general factors such as individual susceptibility factors, biological factors, and psychosocial environmental factors of depression in adolescence, but will also examine the pathological factors, illness perception factors, diagnosis and treatment factors, and symptom-related factors of PCOS, as well as the outcome of depression. LASSO will be used to fit a multivariate warning model of depression risk. Data collected between January 2022 and August 2022 will be used to develop and validate the model internally, and data collected between September 2022 and December 2022 will be used for external validation. We will use the C-statistic to measure the model's discrimination, the calibration plot to measure the model's risk prediction ability for depression, and the nomogram to visualize the model.

**Discussion:**

The ability to calculate the absolute risk of depression outcomes in adolescents with PCOS would enable early and accurate predictions of depression risk among adolescents with PCOS, and provide the basis for the formulation of depression prevention and control strategies, which have important theoretical and practical implications.

**Trial registration number:**

[ChiCTR2100050123]; Pre-results.

## Introduction

Polycystic Ovary Syndrome (PCOS) is a female endocrine metabolic disease of unknown etiology, with a prevalence of 5.6 to 11.04% in adolescence (1) and 10.26% in the Chinese adolescent population (2). Symptoms of PCOS include abnormal menstruation, infertility, hyperandrogenismia, and polycystic ovarian changes (3). It has been controversial and challenging to diagnose PCOS during adolescence due to the overlap between regular pubertal physiological changes (irregular menstrual cycles, acne, and polycystic ovarian morphology on pelvic ultrasound) and adult PCOS diagnostic criteria. Consensus statements on adult and pediatric health have acknowledged these challenges (4–6). To be more specific, challenges include the risk of under-diagnosis, delayed and/or poor diagnosis experiences (7), and over-diagnosis, as well as the additional risk of the use of inconsistent non-evidence-based approaches to PCOS diagnosis and management (8). PCOS generally begins after the first menarche in adolescence and lasts through the reproductive years and perimenopause. Besides affecting reproductive health, PCOS increases the risk of diseases such as type 2 diabetes, cardiovascular disease and endometrial cancer (9), as well as the development of psychiatric disorders. Adolescent girls with PCOS are 2.4 times more likely to suffer from depression than normal girls of the same age, about 50–60% (10, 11). A depressive disorder can result in great psychological and physical distress in adolescents, leading to suicide in over half of them, and it can affect the health and psychosocial functioning of adults as well (12). Studies have shown that PCOS can also lead to infertility in the long run (13). Nevertheless, recent studies suggest that PCOS on its own is not necessarily a cause of infertility (14). It is possible that infertility can be exacerbated by emotional and psychiatric problems in PCOS patients due to illness and fear of future infertility (14). Thus, it is recommended that psychological, emotional, and other non-medical measures be optimized in order to treat infertility, as well as increasing the attention given to depression in individuals with PCOS. PCOS, however, has no identified etiology and no specific treatment. Life management is recommended by international evidence-based guidelines as the ideal treatment for PCOS (15), but patients with the disorder have poor life management skills (16). The guideline declares that patients with PCOS can participate in better life management by improving their psychological status (4). There is no doubt that depression is a significant health issue that must be addressed in the management of adolescents with PCOS.

Depression high-risk groups are individuals or subgroups who suffer from certain depressive symptoms but do not meet the diagnostic criteria for depression (17). They constitute a mental sub-health state between health and depression. Given the high prevalence of depression in adolescents with PCOS, warning of its onset risk and identification of high-risk groups is significant for preventing its development and improving its prognosis (18). There is currently no early detection approach for high-risk groups of depression in adolescents with PCOS, and most routine screening uses questionnaires. Hence, it's necessary to develop a warning model to identify adolescents with PCOS at high risk for depression.

The development of warning models often involves the incorporation of influencing factors. However, a variety of factors affect depression in adolescents, including: (i) biological factors, such as hormones and individual development during adolescence, which modifies neuroendocrine regulation and brain structure in diverse ways, contribute to adolescent depression. For instance, altering the activity of the hypothalamic-pituitary-adrenocortical (HPA) axis, affecting the release of neurotransmitters, altering the REM sleep latency, and so on, can all have an impact on the neurological structure and psychological state of the adolescent population, eventually leading to depression (19); (ii) individual susceptibility factors, such as genetic factors, with heredity influence approximately 40–50% of depressed people. Depressed people's first-degree relatives have a 10–13% chance of developing depression (20); (iii) psychosocial environmental factors, such as family environments, social development and social role changes, and negative behavior patterns, contribute to a sense of helplessness, which leads to negative attributions and ultimately to depression in the long run (21). PCOS may also be associated with several factors, such as insulin resistance and obesity, which may further aggravate the endocrine disorder during adolescence and increase the dysregulation of the HPA axis. Likewise, PCOS also leads to higher levels of androgen in the body, which is closely related to the risk factors of mental diseases (22), so there is speculation that pathological factors such as insulin resistance, obesity and high levels of androgen play a role in the occurrence of depression in PCOS (23). Hormonal drugs, like Ethinylestradiol cyproterone acetate tablets, are often used to treat PCOS. These drugs affect the cortical and subcortical areas of the brain that control emotions. These areas are immature and oversensitive in adolescents, which greatly increases the risk of depression (24). A lack of control over menstrual irregularities (11), as well as a lack of knowledge and information about the disease, which increases the psychological burden of the patients and may worsen depression (25). It can be seen that depression in PCOS is linked to the above-mentioned factors directly or indirectly. It's difficult to predict depression risk from one or more of these factors with any certainty because the number and magnitude of influencing factors are still inconclusive (Figure 1). Thus, developing a warning depression model for adolescents with PCOS through the interaction of complex influencing factors is a critical problem that requires immediate research, and there is no such report currently available.

**Figure 1 F1:**
[figure not shown]
Simulation map of risk factors for depression in adolescents with PCOS.

As previously noted, the occurrence of depression in adolescents with PCOS involves multiple dimensions and contains numerous independent variables. To minimize the bias caused by the absence of important independent variables, it's important to select as many variables as possible at the beginning of the warning model construction process. Traditional regression analysis methods using statistical software such as SPSS, Jamovi, etc., can quantitatively analyze the strength of a predictor based on the regression coefficient. However, conventional regression analysis methods cannot handle collinearity problems and produce high variance when there are numerous independent variables. Least Absolute Shrinkage and Selection Operator (LASSO) is a type of machine learning method introduced by Tibshiran in 1996 (26). On the one hand, LASSO can select features automatically. When there are numerous independent variables, LASSO can selectively integrate powerful explanatory factors into the model. On the other hand, LASSO can compress the coefficients of some minor or insignificant independent variables to zero and pick more relevant independent variables to prevent overfitting. As compared to traditional regression analysis methods, LASSO can process all independent variables simultaneously, which greatly increases the model's stability. LASSO has been gradually applied to the development of warning models in the medical area in recent years (27, 28), as it offers high stability, fast calculation speed, and ease of interpretation in building warning models. To date, LASSO has been applied to the construction of diagnostic prediction models, early risk identification of ischemic stroke, for example (27). LASSO has also been applied to the construction of prognostic prediction models, for instance, survival after ampullary adenocarcinoma resection (28). Additionally, a study based on LASSO used electronic primary care data to develop a predictive model of common mental disorders among adolescents and early adults (29). But the study noted that primary care data underestimated common mental disorders. Due to race and PCOS, the model cannot predict depression with PCOS in adolescents. Thus, we will explore the causes of depression in teenagers with PCOS and the influence of a variety of risk variables, as well as develop and test a depression risk prediction model for adolescents with PCOS. Not only will this model be able to identify high-risk groups for depression with PCOS in adolescence, but also for high-risk groups of depression in general adolescent girls.

## Objectives

The aims of the study are to: (i) Develop a depression prediction model for adolescents with PCOS to identify at-risk populations early; (ii) Validate the accuracy and validity of the model and to assess the clinical utility of the model.

## Methods and analysis

### Preparation

A multidisciplinary research team was established, consisting of obstetricians and gynecologists (*n* = 2), psychiatrists (*n* = 2), psychologists (*n* = 1), nursing specialists (*n* = 1), statisticians (*n* = 1) and research assistants (*n* = 2). Members of the research team have received uniform training in PCOS clinical practice and adolescents as well as extensive experience in their respective fields. Firstly, the team derived an understanding of depression among adolescent PCOS patients by retrieving evidence-based information and integrating clinical practices. Secondly, the research team reviewed the factors associated with depression in adolescents in the general population, and then the pathological factors of PCOS, the perception factors of PCOS, the diagnosis and treatment factors of PCOS, and the symptoms-related factors of PCOS, to summarize the risk factors for depression in adolescents with PCOS.

### Study design

We will use a retrospective cohort design for predictive model development and validation studies. It will follow expert guidance on model development and validation (30, 31), and reported per the Transparent Reporting of multivariable prediction model for Individual Prognosis or Diagnosis (TRIPOD) statement (32).

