### Patient recruitment

Adolescents with PCOS who attend the gynecology clinic of the Affiliated Hospital of Zunyi Medical University from January 2022 to August 2022 will be selected as the potential participants using a consecutive enrollment method. The final participants will be identified based on inclusion and exclusion criteria, and data are collected as both a training dataset and a validation dataset for the model construction. Data collected from September 2022 to December 2022 as an external validation cohort. Participants listed above will comprise the experimental group. Additionally, a control group will be recruited from the gynecology clinic among healthy, age-matched adolescent girls.

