#### Dependent variables

Depression will be measured by the Chinese version of the Children's Depression Scale(CDI) (38). The scale is comprised of 27 items, each of which offers three possible replies based on the respondent's actual mood during the previous 2 weeks. The project consists of five dimensions: anhedonia, poor efficacy, low self-esteem, negative emotions, and interpersonal problems. The intensity of each item determined whether it was rated zero, one, or two, and the negative word statement was scored in reverse. A score of 19 indicated the presence of depressive symptoms. It has been reported that the Chinese version of the CDI scale has been applied to children and adolescents ranging from 7 to 18 years of age in China (38–40). CDI has the advantage of having the lowest reading level of all depression measurement tools (only the first grade level). The Chinese version of the CDI scale has a good level of reliability and validity, as well as a high clinical diagnostic value for depression, and can be used to measure depression in children and adolescents in China. Utilize the total score to reflect the severity of depressive symptoms or diagnostic threshold due to its operability and clinical applicability.

We will use the Kiddie-Schedule for Affective Disorders and Schizophrenia-Epidemiological version (K-SADS-E) to confirm the diagnosis of depression and exclude possible comorbidities. The validated Mandarin version will be used in this study (41). It is a semi-structured diagnostic interview questionnaire designed to assess the current and past mental health status of children and adolescents aged 6-18 in accordance with the diagnostic criteria of the Diagnostic and Statistical Manual of Mental Disorders, 5th edition (DSM-5). In this study, two psychiatrists trained in K-SADS-E interview harmonization will conduct interviews to diagnose depression and exclude possible comorbidities. It will take approximately 1–1.5 h for each participant and their parents to complete the interview. It has been demonstrated that K-SADS-E has good psychometric properties (41). The diagnoses of K-SADS-E demonstrated good convergent and divergent validity with most corresponding clinical questionnaires.

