### Data collection

Two uniformly trained researchers will identified participants based on inclusion and exclusion criteria. Firstly, a researcher will guide participants and their parents to a quiet outpatient room that is conducive to dialogue and data collection. Another researcher will explain the purpose, significance, and implementation of the study to participants and their parents in a one-on-one format, assuring them that their privacy would be protected. With the consent of participants and their parents, researchers will sign informed consent forms with them. Afterwards, psychiatrists within the study team will conduct semi-structured interviews with participants and their parents, focusing on the diagnosis of depression and excluding possible comorbidities. The researchers will distribute the QR code of the scale that was included in the questionnaire platform in advance to participants who are eligible, and the participants will scan the QR code on WeChat to fill out the form online. Finally, the researchers will give the participants health education and prescription advice, as well as recording laboratory indicators including sex hormones and insulin. The total planned time for this process will be around 2 h. The data will be extracted *via* a questionnaire platform and collated into Excel format, with the two researchers collecting the information independently and negotiating any disagreements.

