## Discussion

This research protocol aims to construct and validate a warning model for depression in adolescents with PCOS. It will answer three questions: what factors influence depression risk in adolescents with PCOS; what role do various types of depression risk factors play in the development of depression in adolescents with PCOS; and how interpretable and accurate is the LASSO-based warning system.

There are many factors associated with depression in adolescents with PCOS. For the first time, a depression warning model will be constructed that takes into account not only general factors like individual susceptibility factors, biological factors, and psychosocial environmental factors of depression in adolescence, but also the pathological factors, illness perception factors, diagnosis and treatment factors, and symptom-related factors of PCOS. This study will precisely and early identify depression at-risk groups for PCOS in adolescence by including the influencing factors of several dimensions of depression into the model and leveraging LASSO's ability to automatically screen variables and boost model interpretability.

So far, it has been difficult to identify adolescents at high-risk of depression, which has a severe impact on adolescent mental health. In this study, the research population consists of adolescents with PCOS, who have a significantly greater prevalence of depression and more complicated impacts than general adolescent girls, an important representative sample. Through this study, we hope to remove the bottleneck of identifying adolescents at risk of depression. The success of this study can not only identify the high-risk groups of depression in adolescents with PCOS, but also demonstrate the risk factors and key links associated with depression in adolescents with PCOS. At the same time, it can be extended and applied to the management of high-risk groups of depression throughout adolescent girls, thereby contributing to reducing the prevalence of depression in adolescent girls and implementing comprehensive and effective prevention measures.

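### The study is labelled a retrospective cohort but measures depression and its predictors at a single visit, so the model can estimate only concurrent depression and cannot support onset, early-prediction or causal claims

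*Protocol article*

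**What the plan says.** The design label, in Study design, is: "We will use a retrospective cohort design for predictive model development and validation studies". The same section commits to reporting under TRIPOD, whose name as given there covers both prognosis and diagnosis.

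The procedure is in three other sections:

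- **Patient recruitment.** Girls with PCOS attending the gynecology clinic in 2022 "will be selected as the potential participants using a consecutive enrollment method". January to August supplies the development data and September to December the temporal validation data.
- **Data collection.** After consent, "psychiatrists within the study team will conduct semi-structured interviews with participants and their parents, focusing on the diagnosis of depression". Then "the participants will scan the QR code on WeChat to fill out the form online", and laboratory values are recorded last. The whole process is planned to take about 2 hours.
- **Dependent variables.** The CDI is answered "based on the respondent's actual mood during the previous 2 weeks". The K-SADS-E interview, used to confirm the diagnosis, covers current and past mental health.

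The claims are in the Abstract, Introduction, Objectives and Discussion. The Abstract says that the work would "enable early and accurate predictions of depression risk among adolescents with PCOS". Aim (i) in the Objectives is early identification of at-risk populations. The Introduction motivates the model by the risk of onset and says that causes will be explored. The Discussion lists among the questions to be answered "what role do various types of depression risk factors play in the development of depression in adolescents with PCOS".

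**The concern.** A retrospective cohort needs predictor status fixed at one time and outcome status at a later time, both recoverable from past records or recall. The visit described has one time point and collects its data afresh. If so, every outcome event is a case that already exists when the predictors are measured. The fitted probabilities then describe who is depressed now, not who will become depressed.

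Two things are at stake. First, clinicians given a nomogram presented as an early-warning tool would read its output as a forecast of future risk. Second, predictors that are partly symptoms or effects of depression would be reported as factors in its development.

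**Working it through.** The check is mainly a comparison of sections; little arithmetic applies.

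**1. Is there a second time point?** Data collection describes the visit from consent to the recording of laboratory values, and it contains none. No baseline date, follow-up interval or prediction horizon appears elsewhere in the article. When the blood samples are drawn is not stated, but the values are recorded at this visit.

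**2. Which period does the outcome cover?** The CDI covers the preceding two weeks. The K-SADS-E covers current and past status, and the article does not say whether a past episode counts as an event. On either reading the outcome lies in the present or the past.

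**3. Are girls who are already depressed removed?** Exclusion criteria name cognitive impairment and major mental illness, with schizophrenia, schizoaffective disorder and bipolar disorder as examples. The list is open-ended, but depression cannot sensibly belong to it, because the depression diagnosis is the modelled outcome. The events are therefore existing cases.

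**4. When do the predictors apply (Table 1)?**

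- Referring to earlier time, although recorded at the visit: family history of mental illness, duration of illness, duration of medicine use.
- Measured concurrently and open to influence from mood: sleep (Athens Insomnia Scale), emotion regulation, interpersonal sensitivity, social support, body image, illness perception.

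**5. Does the sample size calculation imply a time horizon?** Inputs from Sample size and calculation: expected proportion 0.4, margin 0.05, multiplier 1.96.

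n = (1.96 / 0.05)² × 0.4 × 0.6 = 1536.64 × 0.24 = 368.79, rounded up to 369.

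The stated 369 reproduces and is not in dispute. It is a precision formula for one proportion at one time, with no incidence or follow-up in it, which fits a cross-sectional reading.

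**6. Would good validation results reveal the problem?** Illustration with assumed inputs, none of them from the article: current depression in 40% of girls shifts a normally distributed predictor (SD 1) upward by d, and the predictor has no effect on later onset. The C-statistic for current depression is Φ(d/√2). The C-statistic for new onset among girls not depressed is 0.50 by construction.

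| Assumed shift d (SD) | C, current depression | C, later onset |
|---|---|---|
| 0 | 0.50 | 0.50 |
| 0.5 | 0.64 | 0.50 |
| 0.8 | 0.71 | 0.50 |
| 1.0 | 0.76 | 0.50 |

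So discrimination that looks useful at the visit is compatible with no ability to predict onset. The temporal validation cohort is assessed in the same way and would reproduce the same C-statistic.

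**The case against.** The strongest defence has four parts.

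**The article already allows for this.** It commits to TRIPOD, which covers diagnostic models, and the Discussion says that prospective cohorts can follow outcomes over time. A concurrent model is a legitimate product. That stands. But the Discussion presents follow-up as making models more robust and names recall as the bias. It keeps the cohort label and never says that the model estimates depression already present.

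**Aim (i) may mean early detection.** The Introduction defines high-risk girls by a present state: symptoms without meeting diagnostic criteria. A concurrent model could partly serve early detection, so a reader who inferred that aim (i) cannot be addressed at all would go too far. The defence does not reach the onset and development wording. It also exposes a further mismatch: the target group does not meet criteria for depression, while the modelled outcome is depression.

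**Some predictors do look backward.** This is correct. A reader might infer that no predictor relates to a time before the outcome window, but Table 1 does not support that. The objection leaves the mood-related scales untouched.

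**The interview-first order is defensible.** A reader might infer that the interview distorts the later answers and that completing the scales first would cure the problem. The documents do not support this. Nothing says that girls are told the diagnosis. In the planned order, psychiatrists reach it before the scale answers exist. The QR code goes to girls found eligible, so the interview appears also to serve as an eligibility step. Reverse causation arises because depression may already be present that day, whichever instrument comes first.

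**Conclusion.** The point holds. The design label contradicts the described procedure, and the onset-risk, early-prediction, causal and developmental claims go beyond what single-visit data can show. The model can estimate the probability of concurrent depression (current, or current and past if past episodes count).

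The size is qualitative. Onset risk is not estimable from this design at any sample size, so there is no corrected figure to give. Multiplying the planned 800 participants by the assumed 0.4 would only restate how many existing cases are expected. The C-statistics above rest wholly on assumed shifts and an assumed absence of effect on onset. They show that the problem could stay hidden, not that it will be of that size.

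The conclusion assumes that the visit described in Data collection is the whole of the assessment, as the article presents it. It does not mean that a model of current depression is without value, or that the order of interview and scales is at fault.

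**What to change.** - **Study design:** restate it as a cross-sectional diagnostic (concurrent) prediction model with newly collected data, reported under the diagnostic TRIPOD items.
- **Predicted quantity:** define it as the probability of current depression at the visit, and label the nomogram accordingly.
- **Objectives, aim (i):** reword as detection of current depression in adolescents with PCOS.
- **Abstract, Introduction and Discussion:** remove the claims about early prediction of risk, onset, causes and role in development. Alternatively, mark them as needing a follow-up study of girls not depressed at baseline, with a stated horizon.
- **Limitations in the Discussion:** state that the mood-related predictors were measured concurrently and that reverse causation cannot be excluded.

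The order of interview and scales can stay as planned. The cost is rewording and a narrower claim; no extra participants, visits or measurements are needed.
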